PROMs can be generic or disease-specific, and each has several advantages and disadvantages [38]. Generic measures are used to compare outcomes across different populations and interventions, particularly for cost-effectiveness studies and health system decision-makers. Disease-specific measures assess the health status of a specific patient population and may be more sensitive for the detection and quantification of changes that are important to clinicians or patients. A common recommendation in clinical research with PROMs is to combine both a generic and a disease-specific measure for use in a particular patient population, especially when PROMs are used to monitor health and how it changes over time. The presumed benefit of this combination is to broaden the scope of measurement and allow for different uses of the measures (e.g., comparison within versus across disease populations). However, evidence to support this recommendation is limited. In fact, in a study examining the usefulness of generic and disease-specific measures of health status in patients with Alzheimer’s, the EQ-5D (a generic measure) was found to be a suitable alternative to a disease-specific measure of health [39]. Another study reported that generic and disease-specific measures performed similarly in assessing changes in HRQL in patients with kidney failure requiring hemodialysis [40]. There is usually some level of overlap between generic and disease-specific measures, and the need for combining both types of measures depends on the target patient population and the constructs assessed by each measure. Given the workload associated with collecting and using PROM data in clinical settings, it is imperative to explore whether one single PROM is sufficient to improve patient-provider communication, processes of care, and ultimately patient outcomes, before recommending the use of a combination of generic and disease-specific measures.

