## Aims of the research

The overall aim of this study is to explore the usefulness of integrating PROM assessments in the clinical management of hemodialysis patients. Specifically, the primary objective is to determine the effects of routine measurement and reporting to clinicians of PROMs, namely, the Edmonton Symptom Assessment System- revised: Renal (ESAS-r: Renal) [43] [44], or the Integrated Palliative care Outcome Scale – Renal (IPOS-Renal) [45] and/or the EQ-5D-5L [46] on patient-reported experience, particularly patient-clinician communication, measured by the Communication Assessment Tool (CAT), for patients with kidney failure requiring hemodialysis. The secondary objectives are as follows:
i.To determine if there is a difference in patient-reported experience and other outcomes induced by a condition specific (ESAS-r: Renal /IPOS-Renal) versus a generic (EQ-5D-5L) PROM;ii.To determine the effects of routinely measuring and reporting the ESAS-r: Renal/IPOS-Renal and/or the EQ-5D-5L on the clinical management of symptoms;iii.To determine the effects of routinely measuring and reporting the ESAS-r: Renal /IPOS-Renal and/or the EQ-5D-5L on overall HRQL;iv.To determine the effects of routinely measuring and reporting the ESAS-r: Renal/IPOS-Renal and/or the EQ-5D-5L on symptom burden, mental health outcomes and healthcare utilization;v.To determine the cost effectiveness of routinely measuring the ESAS-r: Renal/IPOS-Renal and/or the EQ-5D-5L for patients with kidney failure requiring hemodialysis;vi.To explore the perspectives and experience of patients and clinicians with routine measurement and reporting of PROMs in clinical practice.

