## Methods

### Study design

To date, the effect of PROMs on patient outcomes were generally assessed in conventional parallel-group RCTs of individuals. Few convincingly demonstrated benefits to patient-important outcomes, which might be in part due to contamination effects and small sample sizes [47]. This study uses a cluster RCT design, with clustering occurring at the level of individual hemodialysis units, to reduce potential contamination between the study groups (Fig. 1). EMPATHY is an open-label RCT, since blinding is not feasible [48]. Consequently, research staff, clinicians, and all patients are aware of group allocation. Dialysis units, stratified by three regions (Northern Alberta, Southern Alberta, and Ontario), were randomly allocated using random number sequences with all units from a region randomized on the same day. Dialysis units were allocated in a 1:1:1:1 ratio into four groups:
Group 1: Patients complete ESAS-r: Renal or IPOS-RenalGroup 2: Patients complete EQ-5D-5LGroup 3: Patients complete both ESAS-r: Renal or IPOS-Renal and EQ-5D-5LGroup 4: Usual care (i.e. the control group). To assess study outcomes, patients complete the PROMs at baseline, 6 and 12 months, but these data are not reported back to clinicians or patients.

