### Quantitative trial data analysis

The primary analysis will assess change in the overall CAT score, between study groups from baseline to 12 months using a linear mixed effects model, with the mean CAT for the dialysis unit at baseline as a fixed effect covariate, and dialysis unit (cluster) as a random intercept. Ideally, analysis should use individual patients’ baseline CAT and follow-up CAT rather than the unit mean baseline CAT to compute change over time. However, due to concerns by the regional renal programs to maintain anonymity of experience data as well as the natural drop-in and drop-out of patients in the dialysis units due to patient deaths and initiation of new patients onto dialysis, individual CAT surveys were made completely anonymous. As such, our primary analytic plan will be based on changes in mean CAT score at the unit level, from baseline to 12 months. The primary analysis will be based on all of the PROMs intervention groups combined compared to the control (no PROMs intervention) group as fixed effects. Any units that drop-out after randomization but prior to initial data collection will be excluded. We will employ last observation carried forward methods to impute missing data where appropriate. As one of our secondary objectives, assessing differences between specific and generic PROMs, we will compare the individual interventions groups (i.e., ESAS-r: Renal /IPOS alone, EQ-5D-5D alone, or the combination) to the control group.

As part of our secondary analyses, we will also compare the proportion of patients reporting symptoms/problems on the ESAS-r: Renal or IPOS-Renal and EQ-5D-5L and the management of such symptoms/problems. Through clinical records, we will link PROMs scores with the use of specific symptomatic treatments as per the treatment aids. We will obtain medication lists, allied health referrals, and chart notes to capture how symptoms are being treated. Because the PROMs data will be collected as part of the clinical record, and linked with individual patient-level data, we will be able to analyze these data using logistic mixed-effects regression models adjusting for individual patient-level covariates. Each renal program (i.e., AKC-N, AKC-S and ORN) will be analyzed separately then we will use meta-analyses to analyze the data from each renal program.

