## Discussion

The evaluation of PROM interventions such as those described in this protocol can be challenging given the nature of clinical practice in busy hemodialysis units, the variations in organization and clinical workflow across units, as well as regional programs. We will study the implementation of PROM interventions in real-world health settings. Thus, we will adopt a pragmatic approach and accept the necessary variations in implementation, while attempting to retain as many of the core elements of the interventions across the programs. Furthermore, given the desire to maintain anonymity of patient-reported experience, our primary analytic strategy will be limited to comparison of the outcome measures at the group level. These pragmatic approaches to the design of this implementation study limit the rigour of the evaluation of the efficacy of PROM interventions, but on the other hand, enhance our evaluation of real-world effectiveness. Along with the planned qualitative assessments, the information gained from this implementation trial will provide valuable information for the regional dialysis programs in enhancing and sustaining the PROM interventions in the most appropriate manner.

A question that is often raised with the implementation of PROM programs is the choice of the measures. We are choosing to implement a combination of specific and generic measures. While a secondary objective is to compare these types of measures, it is possible that the differences (e.g., breadth or scope) between measures matter less than either approach simply serving as a mechanism for engaging patients and clinicians in a more focused discussion on symptoms or problems. This is the intention with our primary analytic strategy of combining the intervention groups to compare against the control group with no PROM intervention. There may be other reasons, beyond the patient-clinician interaction, however, that guide decisions on the choice of measures. For example, programs may be interested in evaluating the overall quality and efficiency of services, and may therefore be interested in a measure that provide data to support economic evaluation. In this case a generic preference-based measure such as the EQ-5D provides an overall index score compatible with that purpose, which may not be available with measures assessing symptom burden.

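### The secondary objective of comparing disease-specific with generic PROMs is assigned only comparisons with control, which give no test or interval for that difference

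*Protocol article*

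**What the plan says.** In the protocol article, Aims of the research, secondary objective i reads: "To determine if there is a difference in patient-reported experience and other outcomes induced by a condition specific (ESAS-r: Renal /IPOS-Renal) versus a generic (EQ-5D-5L)" PROM. The Discussion repeats the aim: "While a secondary objective is to compare these types of measures".

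The section Quantitative trial data analysis takes up this objective by name, "As one of our secondary objectives, assessing differences between specific and generic PROMs", and in the same sentence gives its analysis: "we will compare the individual interventions groups (i.e., ESAS-r: Renal /IPOS alone, EQ-5D-5D alone, or the combination) to the control group".

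The primary analysis does not separate the PROM arms: "The primary analysis will be based on all of the PROMs intervention groups combined compared to the control (no PROMs intervention) group as fixed effects". The Economic evaluation also takes usual care as its reference. Under Study design, "Dialysis units were allocated in a 1:1:1:1 ratio into four groups": Group 1 is disease-specific alone, Group 2 generic alone, Group 3 both, and Group 4 usual care.

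**The concern.** Objective i is about the difference between Group 1 and Group 2. The analysis assigned to it yields Group 1 minus Group 4, Group 2 minus Group 4 and Group 3 minus Group 4, and nothing with a standard error for Group 1 minus Group 2. This is not a detail left for an analysis plan to fill in. The article commits to an analysis for this objective, and that analysis does not answer it.

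The risk lies in how the results would be read. One comparison with control below 0.05 and another above it is not evidence that the two arms differ, yet the planned output invites that reading. The Discussion says the results will guide PROM use in Alberta and Ontario dialysis units, so a mistaken claim that one instrument works and the other does not could influence the choice of instrument.

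**Working it through.** **Inputs.** From Setting and population and Sample size and power: 44 units, about 3000 patients, ICC 0.1, SD of the CAT 0.74, two-sided α 0.05, and 80% power for an effect size of 0.23. From Study design: allocation 1:1:1:1. Derived: m = 3000/44 = 68.2 patients per unit, and 44/4 = 11 units per arm (arm counts are not stated). Assumed: equal unit sizes, normal approximation, no baseline adjustment, and 0.23 read as CAT points. The protocol does not say whether 0.23 is in points or SD units.

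**The plan's own figure.** Design effect = 1 + (68.2 − 1) × 0.1 = 7.72. For the pooled comparison of 33 with 11 units (2250 with 750 patients), SE = 0.74 × √7.72 × √(1/2250 + 1/750) = 0.0867. Power for 0.23 points is then 75.6%, near the stated 80% but not equal to it. That gap is a separate matter, and nothing below depends on it.

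**One arm against another, or against control.**
- Variance of a unit mean = 0.74² × (0.1 + 0.9/68.2) = 0.0620.
- SE of a difference between two arms = √(2 × 0.0620/11) = 0.106.
- Detectable difference at 80% power = 2.80 × 0.106 = 0.297 points.
- Power for 0.23 points = 58%.

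**Two control comparisons read side by side.** Let both PROMs have the same true effect δ. The two z statistics each have mean δ/0.106 and correlation 0.5, because they share the control arm. The chance that exactly one is significant is:

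| True effect of both PROMs (CAT points) | Power of each v control | Exactly one significant |
|---|---|---|
| 0 | 5% | 8% |
| 0.10 | 16% | 19% |
| 0.17 (0.23 SD: 0.23 × 0.74) | 36% | 31% |
| 0.23 | 58% | 33% |
| 0.30 | 81% | 22% |
| 0.35 | 91% | 12–13% |
| 0.40 | 96% | 6% |

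In every row the direct test of Group 1 against Group 2 is significant in 5% of trials. At δ = 0.23, only about 12% of the discordant trials would also show a significant direct contrast.

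**Baseline adjustment.** The planned model includes the unit's baseline mean CAT. If this removed half the between-unit variance (an assumption), the unit-mean variance would be 0.74² × (0.05 + 0.9/68.2) = 0.0346 and the SE √(2 × 0.0346/11) = 0.079. Exactly one comparison would then be significant in about 20% of trials at 0.23. If it removed three quarters, the figure would be about 6%. At smaller effects adjustment can raise the figure: at 0.10 points, halving the between-unit variance moves it from 19% to about 26%.

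**The opposite error.** With true effects of 0.40 and 0.63 points, both arms are significant against control in 96% of trials, so the pattern shows no difference. The direct contrast detects the 0.23-point difference in 58%.

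**The case against.** Several points on the other side stand.

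- **The point estimate is not lost.** Subtracting two arm effects measured against a common control gives Group 1 minus Group 2. A reader might infer that the trial can never estimate the quantity, but that goes too far. What is missing is the standard error, interval and test, and these cannot be recovered from two separately reported comparisons without their covariance.
- **The one-third figure is not the error rate of a planned test.** No section says that a difference will be concluded from one significant and one non-significant result. The figure describes a reading that the output invites. It is also close to its maximum, so the documents do not support saying without conditions that the plan will often suggest a false difference.
- **Sharing the control arm does not make matters worse.** A reader might list it as a further defect. With independent controls at 58% power, discordance would be 2 × 0.582 × 0.418 = 49%; sharing lowers it to 33%. The control mean also cancels in Group 1 minus Group 2.
- **The question of a single PROM is largely served as planned.** The background says "it is imperative to explore whether one single PROM is sufficient to improve patient-provider communication". A reader might infer that Group 3 must be compared with Groups 1 and 2. But sufficiency to improve communication is addressed by each single-PROM arm against control, and the sentence is rationale, not one of objectives i to vi.
- **The scope is limited.** The Discussion itself suggests that differences between measures may matter less than using either one.

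None of this removes the mismatch between objective i and the analysis assigned to it.

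**Conclusion.** The plan is wrong as written on this point and should be corrected. Objective i asks for a difference between two PROM types, and the analysis named for it supplies no test or interval for that difference. This conclusion rests on the text alone.

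The size of the possible misreading is conditional. With equally effective PROMs and a reader who compares significance verdicts, a false difference would appear in about 33% of trials at 0.23 points (31% if 0.23 is in SD units), and in about 6% to 33% for effects from 0 to 0.40 points. A direct test would give 5%. These figures assume 11 equal units per arm, the stated ICC and SD, and no baseline adjustment. With half the between-unit variance removed, the figure at 0.23 is about 20%.

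The error concerns one secondary objective. The pooled primary comparison is untouched.

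**What to change.** In Quantitative trial data analysis, replace the sentence on this secondary objective with wording to this effect:

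- Fit the linear mixed model with a four-level arm term. For objective i, report Group 1 minus Group 2 with its 95% CI.
- Keep each arm against control as supportive.
- State that no difference between PROMs will be inferred from the p-values of the control comparisons, and that a non-significant direct contrast is not evidence of equivalence.

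Group 3 minus the mean of Groups 1 and 2 may be added if the sponsor wants to know whether the combination adds anything. It is optional.

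The cost is one contrast statement. No further units, patients or measurements are needed. The drawback is a wide interval: without baseline adjustment the detectable difference is about 0.30 CAT points, and the 95% half-width is about 1.96 × 0.106 = 0.21 points. That is the precision the design has for this question.

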### Economic evaluation

A cost-effectiveness analysis will be employed of the different study groups, compared to the usual care group as the reference case. The incremental costs and incremental QALYs of the different interventions relative to the usual care group will be compared to calculate incremental cost per QALYs gained ratios [60, 61]. Costs will be estimated for patients in the different study groups, including treatments received by patients, taking the perspective of the provincial health care system, personnel costs for training and delivery of the PROMs assessments, and subsequent health care utilization for patients in each of the study groups. Health care utilization will be estimated through linkage with provincial administrative health care databases at the individual patient-level. Costs associated with provision of the intervention, including training and nursing time, will be estimated through observations for time and valued using standard staffing wage scales for the respective geographic regions. QALYs will be calculated based on changes in the EQ-5D-5L index score, using the Canadian preference weighting [62]. Discounting or inflationary factors will not be applied as the analysis will be limited to the period of the study itself (i.e., 12 months). Self-reported survey and clinical data will be linked to administrative data on healthcare utilization (e.g., number of hospitalizations, number of emergency department visits, number of family physician and specialist visits, cost), one-year prior and one-year after the intervention starts. Linkage to lab and medication datasets will also be performed where available.

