## Study timelines

The three renal programs implemented EMPATHY on different timelines. AKC-N implemented EMPATHY in September 2018 with all units starting at once. AKC-N completed the 1-year trial period in October 2019. AKC-S and ORN implemented EMPATHY with a phased approach, meaning groups of units started the trial at different points. AKC-S started phasing units into the trial in January 2019 and ORN in April 2019. ORN and AKC-S will complete the trial by the end of 2020.

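### Cost-effectiveness ratios are defined for each PROM arm against usual care alone, so they cannot show which of the four strategies is efficient

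*Protocol article*

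**What the plan says.** The Economic evaluation section sets the comparator: "A cost-effectiveness analysis will be employed of the different study groups, compared to the usual care group as the reference case". It then defines the cost-per-QALY ratios from the "incremental costs and incremental QALYs of the different interventions relative to the usual care group". It names no comparison among the three PROM arms, no ranking or dominance step and no decision rule. The Quantitative trial data analysis section does likewise for effectiveness: each intervention group is set against control, even for the objective of contrasting specific with generic measures.

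Under PROMs in clinical practice, the article cites the workload of PROM collection and says that the sufficiency of a single PROM must be explored "before recommending the use of a combination of generic and disease-specific measures". Aims of the research lists specific versus generic as secondary objective (i) and cost-effectiveness as objective (v).

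On prices, the Economic evaluation section says: "Discounting or inflationary factors will not be applied as the analysis will be limited to the period of the study itself (i.e., 12 months". It states no price year. The Study timelines section says "AKC-N implemented EMPATHY in September 2018 with all units starting at once", that the other two programs phased units in from January and April 2019, and that "ORN and AKC-S will complete the trial by the end of 2020".

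**The concern.** A renal program can adopt only one of the four strategies. The useful question for each is what the extra QALYs cost compared with the next cheaper option worth considering. A ratio against usual care averages over all the gain since no PROM. If a single PROM already delivers most of that gain cheaply, the average hides the price of the last small step to using both. An arm that costs more and yields less than another PROM arm can still have a favourable ratio against usual care.

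The Discussion says the results will guide PROM use in Alberta and Ontario dialysis units. If the ratios are read as they are defined, a program could adopt the combination because it yields the most QALYs at an acceptable ratio, or the arm with the lowest ratio. Neither need be the efficient choice.

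The reason given for not adjusting prices is a separate, smaller matter. Twelve months is the horizon for each unit, not the calendar span over which costs arise.

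**Working it through.** The article gives no cost, QALY, threshold or ratio, so there is no figure of its own to reproduce. All costs, QALYs, thresholds, inflation rates and start-date imbalances below are assumptions. The dates, unit counts and stratification come from the article.

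**1. Shared comparator, two PROM strategies.** Assumed increments against usual care:
- generic: +$100 and +0.010 QALY
- both: +$400 and +0.012 QALY

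Ratio = incremental cost / incremental QALY.
- generic against usual care: 100 / 0.010 = $10,000
- both against usual care: 400 / 0.012 = $33,333
- both against generic: (400 - 100) / (0.012 - 0.010) = 300 / 0.002 = $150,000

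**2. All four strategies.** Assumed increments against usual care, with net benefit = 60,000 × QALY - cost at an assumed threshold of $60,000:

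| Strategy | Cost | QALY | Ratio against usual care | Ratio against next cheaper | Net benefit |
|---|---|---|---|---|---|
| Generic | 150 | 0.009 | 16,667 | 16,667 (usual care) | 540 - 150 = 390 |
| Specific | 200 | 0.010 | 20,000 | 50 / 0.001 = 50,000 | 600 - 200 = 400 |
| Both | 450 | 0.012 | 37,500 | 250 / 0.002 = 125,000 | 720 - 450 = 270 |

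All three arms pass the threshold against usual care. The lowest ratio points to generic, and the most QALYs under the threshold points to both. Net benefit and the sequential ratios point to specific.

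**3. Calendar span.** September to December 2018 is 4 months. Adding 2019 and 2020 gives 4 + 12 + 12 = 28 months of follow-up. Utilization is also linked for "one-year prior and one-year after the intervention starts", which takes the linked data to 28 + 12 = 40 months.

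**4. Price drift between programs.** From the middle of the AKC-N year to the middle of the latest possible year (calendar 2020) is about 1.29 years. At an assumed 1-3% a year: 1.01^1.29 - 1 = 1.3% and 1.03^1.29 - 1 = 3.9%.

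**5. Price drift between arms.** Allocation was stratified by region and AKC-N units started together, so only the phased-start units can contribute: 12 AKC-S + 15 Ontario = 27 of 44. If mean start dates in those units differ between arms by d months, the effect as a share of mean cost is ((1 + r)^(d/12) - 1) × 27/44. This treats units as equal in cost.
- r = 1%, d = 1: 0.083% × 0.614 = 0.05%
- r = 3%, d = 6: 1.489% × 0.614 = 0.91%

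At an assumed annual cost of $50,000 per patient, that is about $25 to $457.

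**The case against.** The strongest reply on the comparator is that nothing is lost. Increments against a common comparator give every pairwise increment by subtraction, as step 1 shows. The article does not forbid comparisons among PROM arms, and dominance rules and net benefit are often left to a separate analysis plan. What stands is that the data suffice and a fuller plan may go further. But the article does not merely stay silent; it states which ratios will be calculated, and those do not answer the choice among arms. Subtraction shows the repair is cheap, not that the stated ratios are the right ones.

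It can also be said that the background passage on a single PROM concerns communication, care processes and outcomes rather than cost, and that the primary analysis pools the PROM arms. Both are true. Yet the motive given there is workload, a resource matter, and the economic evaluation keeps the arms separate.

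The worked figures were chosen to show a reversal. They show that one is possible, not that it is likely.

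On prices, a reader might infer that the plan will add costs from 2017 to 2020 in mixed prices and so pick the wrong arm. The article does not support that. It names no price year, and wage scales or unit costs could all come from one year. The year before start is described as linked data, and nothing shows it entering the 12-month ratio. Stratification by region makes most drift common to all arms.

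**Conclusion.** The comparator point holds. Followed as written, the economic evaluation cannot show which strategy is efficient or whether the combination justifies its cost over one PROM. Its size cannot be fixed from the article; the examples show only how far a ratio against usual care can depart from the relevant one. *Only* against usual care is a reading of the text as it stands, since no other economic comparison is named.

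The price-year point is second-order. A 12-month horizon supports no discounting but does not support leaving out a common price year across 28 months of follow-up. The between-arm effect is likely below 1% of mean cost under the stated assumptions. In dollars, the top of that range is not trivial beside the small increments assumed above, but it needs a start-date imbalance that the article does not report. The risk of choosing the wrong strategy rests on the comparator, not on price years.

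**What to change.** Replace the ratio sentence in the Economic evaluation section with a full incremental analysis:
- rank the four strategies by mean cost;
- remove dominated and extendedly dominated strategies;
- report each remaining ratio against the next less costly option;
- report net benefit per arm, with the probability of being best, at stated thresholds.

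Ratios against usual care can still be reported alongside.

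Replace the inflation clause with one stated price year in which all costs are expressed, and keep the decision not to discount.

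The cost is a change of analysis wording and reporting plus a price-index step. No new data are needed.
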